### OAT follow-up phase

After the first 7 days, OAT will be prescribed at intervals and doses adjusted as indicated according to the standard clinic protocols, and dispensed by a community pharmacy of the participant’s choosing.

Participants will be asked to refrain from using prescribed opioids for safer supply during the first 7 days of the study, but thereafter concomitant care and interventions will be provided as clinically indicated.

## Outcomes and assessments

### Timeline of assessments

Tables 1, 2, 3

**Table 3 Tab3:** Schedule of assessments during OAT follow-up phase (months 1–12)

	1 month	3 months	6 months	12 months
Currently on oral OAT? (Yes/no)	x	x	x	x
Current OAT type and dose	x	x	x	x
Participant satisfaction (MSQ for OUD meds)	x	x	x	x
Self-reported use of illicit opioids/other substances	x	x	x	x
Clinic attendance	x	x	x	x
COWS	x	x	x	x
UDT	x	x	x	x
Overdose events req. intervention	x	x	x	x
Hospitalizations/death	x	x	x	x

*OAT* opioid agonist therapy, *UDT* urine drug test, *COWS* clinical opiate withdrawal scale, *MSQ* Medication Satisfaction Questionnaire, *OUD* opioid use disorder

### Primary outcome

The primary outcome of this study is safety, as defined by occurrence of study drug-related adverse events (including but not limited to sedation, respiratory depression, hypoxia, QT interval prolongation) requiring intervention during the induction and early OAT phases (study days 1 through 7).

The participant’s level of sedation (POSS) and vital signs (heart rate and oxygen saturation by pulse oximetry, blood pressure, and respiratory rate) will be monitored before starting induction, throughout the induction phase, at 5, 10, and 15 min (or until stable) after the final IV fentanyl dose, before the starting dose of OAT is administered, and hourly during the initial 3 h following oral OAT administration. In addition, sedation and vital signs will be assessed once daily for the first 7 days after the initial OAT dose, and during OAT follow-up at 1 month, 3 months, 6 months, and 12 months (Table 3).

In case of suspected opioid overdose (excessive sedation [POSS 3 or 4], respiratory rate below 8 breaths per minute, oxygen saturation below 92% or the participant’s baseline, and/or other signs or symptoms) at any time during the induction or OAT phases or during OAT follow-up, no further IV fentanyl doses will be administered and management will commence immediately according to the clinic overdose response protocol, consistent with established local and provincial guidelines [25].

Oral methadone can cause prolongation of the QTc (heart rate-corrected QT interval), which in turn is a risk factor for a rare but potentially fatal arrhythmia, Torsades de Pointes (TdP) [26]. An electrocardiogram (ECG) will be performed before commencing the induction and the results will be considered, along with other TdP risk factors, in the clinical decision-making process of selecting methadone or SROM as the appropriate OAT option for that individual [26, 27]. Participants who will receive methadone in this study will be advised during the informed consent process that the risk of arrhythmia is increased with higher doses of methadone. The first 7 days after starting methadone is the time of maximum risk of clinical adverse events, with a peak risk on Day 3 [28]; therefore, an ECG will be repeated on OAT Days 3 and 7 for participants receiving methadone. Any occurrence of QTc prolongation (> 500 ms, or ≥ 60 ms increase from baseline) and/or symptoms consistent with TdP will be managed promptly, consistent with recommendations in national OUD treatment guidelines [27].

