## Study design

### Overview of study design

To assess the safety, feasibility, and efficacy of a rapid symptom-inhibiting IV fentanyl induction (SIFI) protocol, we plan to conduct an open-label, single arm, prospective clinical trial with a planned sample size of 50. The primary goal of this pilot study is to identify unforeseen problems with the SIFI procedures that would impact participant safety. If such a problem exists with a prevalence of 5% (i.e. potential to affect 1 out of 20 participants), it will be identified with 92% confidence in a pilot study including 50 participants [15].

Results of this pilot study will be used to inform a subsequent larger and more comprehensive investigation of the SIFI protocol as a treatment strategy for individuals with OUD who intentionally use unregulated fentanyl.

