### Study objectives

The primary objective is to assess the safety and feasibility of an outpatient SIFI protocol for determining individualized starting doses of oral OAT with methadone or SROM. Safety will be assessed in the first instance by a descriptive analysis of adverse events (e.g. sedation, respiratory depression, hypoxia, QT prolongation) requiring intervention during the induction/maintenance period (study days 1 through 7).

Secondary outcomes include starting OAT doses, participant satisfaction, and presence of withdrawal symptoms, OAT retention, overdose, hospitalization, and death at 1 and 3 months. Longer term impact of the strategy will be assessed at 6 and 12 months post-induction. Secondary outcomes will be reported using descriptive and summary statistics. Participants’ responses to the treatment satisfaction questions will be reported qualitatively, and used to refine the SIFI procedure for future investigation.

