## Data analysis and management

The primary safety outcome will be assessed in the first instance by a descriptive analysis of adverse events requiring intervention during the induction and early OAT phases of the study. Secondary outcomes will be reported using descriptive and summary statistics. Participants’ responses to the treatment satisfaction questions will be summarized, and the results used to refine the SIFI procedure for future investigation.

Participants are assigned unique study codes that are not derived from or related to their personal information. Study-related documents, biological specimens, and ECG reports will be labelled only with the participant’s unique study code, and not with their name, initials, or other identifying information. All study documentation will be kept in a secure area in locked cabinets.

Files that contain personal identifying information are kept securely in locked offices in electronic form, and access to these files are password restricted to the principal investigator and a limited number of designated research team members. Identifying information collected on the questionnaires will be removed and stored separately from the questionnaire responses. Participant consents and contact information for follow-up will also be stored separately in a secure area in locked cabinets.

Electronic data will be stored on a secure server. For this study, clinical and sociodemographic information will be drawn from routinely collected clinic and administrative data in the clinic electronic medical record (EMR). Clinicians and research staff access the EMR via a roles-based, credentialed, secure portal to the EMR system.

Data in the clinic EMR database is under the custody of the British Columbia Centre for Excellence in HIV/AIDS ([name]) and its Director, [name] (a co-investigator on this study). The EMR database is stored on a secure server on the Centre’s network, protected by a defense-in-depth system including an industry-standard firewall prohibiting unauthorized entry. Strict measures are in place to protect the privacy of individuals in the database. The Centre also utilizes a suite of privacy and security policies to ensure the proper protection, management and integrity of all data. All data will be de-identified for study analyses to limit the potential for disclosure of identifying information.

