## Discussion

This is the first study to objectively estimate opioid tolerance and use it to determine individualized starting doses of oral OAT for use in an outpatient setting among people who use unregulated fentanyl. This study was initiated in response the inadequacy of current OAT dosing recommendations to address the increasing contamination of the unregulated drug supply with high-potency opioids, mainly fentanyl and its analogues, resulting in an ongoing crisis of opioid overdose and death in BC and elsewhere.

The SIFI procedure involves an IV induction with medical fentanyl, guided by pharmacological principles [33, 34], and has been implemented successfully in an in-hospital setting [3]. To optimize participant safety in this outpatient study, participants will be closely supervised in the clinic during and after the IV fentanyl induction procedure.

A limitation of the SIFI protocol is that sedation observed during the induction procedure may be due to other factors in addition to medically-administered IV fentanyl. In a setting where multi-substance use is common, other contributing factors may include prescription, non-prescription, or unregulated sedating substances (e.g. benzodiazepines, alcohol), and/or catecholamine depletion as a consequence of chronic use of methamphetamine or other stimulants. Operationally, any somnolence or lethargy observed during the induction procedure is attributed to the administered IV fentanyl. If additional sedating factors are present, the consequence would be to underestimate the participant’s opioid tolerance and administer too low a dose of methadone or SROM to fully meet their opioid requirements. This limitation is unavoidable in the interests of participant safety in a setting where the potential effects of concomitant sedating substances cannot be determined or quantified.

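### The primary safety outcome is stated with and without a drug-relatedness condition, and the narrower count rests on a judgement for which the article gives only a partial rule

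*Protocol article*

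**What the plan says.** **Where the relatedness condition appears.** The Primary outcome section gives "safety, as defined by occurrence of study drug-related adverse events (including but not limited to sedation, respiratory depression, hypoxia, QT interval prolongation) requiring intervention", over study Days 1 through 7. The Methods part of the Abstract defines the outcome with the same two conditions, drug-related and requiring intervention. Under Monitoring, the second hold trigger also counts study drug-related events that need intervention, with limits of 5 of the first 10 participants, 10 of 20, 15 of 30 and 20 of 40.

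**Where it does not.** Study objectives states: "Safety will be assessed in the first instance by a descriptive analysis of adverse events", limited to those requiring intervention on Days 1 to 7, with no mention of relatedness. Data analysis and management says the primary safety outcome will be assessed by a "descriptive analysis of adverse events requiring intervention during the induction and early OAT phases of the study", again without it.

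**On attribution.** The Discussion says that "the potential effects of concomitant sedating substances cannot be determined or quantified". It says so while explaining why opioid tolerance may be underestimated, and it adds a working rule: somnolence or lethargy seen during induction is put down to the IV fentanyl. The Exclusion criteria section does not exclude users of other substances.

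**Design and size.** The trial is an "open-label, single arm, prospective clinical trial with a planned sample size of 50". On size, Overview of study design supposes a safety problem with 5% prevalence and claims that "it will be identified with 92% confidence in a pilot study including 50 participants". Monitoring states that there is no independent board and that the investigators follow adverse events.

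**The concern.** The endpoint has two numerators. Under one, an event needing intervention counts only if it is judged related to study drug; under the other, it counts whatever its cause. Data analysis and management is where the count is to be made, and it carries the wider wording.

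The narrower count is the more fragile one here. With no control group there is no background rate against which to judge cause, and other sedating substances are expected. The article's one attribution rule stops at the end of induction and covers only somnolence or lethargy. It gives none for respiratory depression, hypoxia or QTc, and none for the days after induction, when participants leave the clinic between visits. For methadone, the Primary outcome section itself calls the first 7 days the period of greatest risk.

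At stake are the reported primary rate, the meaning of the 92% figure when applied to that rate, and the input to one of the two hold triggers.

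**Working it through.** **1. The wordings side by side**

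| Section | Drug-related required? | Intervention required? |
|---|---|---|
| Abstract, Methods | Yes | Yes |
| Primary outcome | Yes | Yes |
| Monitoring, second hold trigger | Yes | Yes |
| Study objectives | Not stated | Yes |
| Data analysis and management | Not stated | Yes |

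The intervention condition is the same in all five places. Only relatedness differs.

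**2. The plan's own figure.** Inputs from Overview of study design: n = 50, prevalence p = 0.05. The chance of at least one case is 1 − (1 − p)^n = 1 − 0.95^50 = 0.9231. The stated 92% is reproduced.

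**3. Sensitivity of that figure.** Let q be the share of true events that enter the primary count, meaning that they are judged related and treated as having required intervention. The document gives no q, so the values below are assumptions. The chance of at least one counted case is 1 − (1 − 0.05q)^50.

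| q (assumed) | 0.05q | Chance of at least one counted case |
|---|---|---|
| 1.0 | 0.050 | 92.3% |
| 0.9 | 0.045 | 90.0% |
| 0.8 | 0.040 | 87.0% |
| 0.7 | 0.035 | 83.2% |
| 0.5 | 0.025 | 71.8% |

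**4. The participant-count hold trigger.** This was computed as an exact sequential binomial over the four looks (5/10, 10/20, 15/30, 20/40), with independent participants and a per-participant counted rate of (true rate × q). The true rates are also assumptions.

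| True rate (assumed) | q = 1 | q = 0.8 | q = 0.5 |
|---|---|---|---|
| 30% | 16.6% | 7.0% | 1.0% |
| 50% | 80.0% | 45.5% | about 8% |
| 60% | 97.3% | 73.9% | 16.6% |

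Steps 3 and 4 show how the count would respond to missed events. They do not show that events will be missed. If events were attributed to study drug too readily, the count would move the other way.

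**The case against.** **The two wordings may be one.** Data analysis and management refers to the primary safety outcome, which is defined elsewhere, and Study objectives is a short statement. Neither says that all events count regardless of cause. Shorthand is a fair reading, but nothing on the page settles it, and the sentence describing the analysis is the wider one. The objection lowers the gravity; it does not remove the need to align the text.

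**A reader might infer that the document admits attribution cannot be made.** It does not. The Discussion says that the effects of co-used sedatives cannot be quantified, in the context of tolerance, and assigns induction somnolence to fentanyl. Carried over to event counting, that rule would over-attribute. So it cannot be said that the conditions always push the rate down.

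**A reader might infer that a threshold crossing could simply be watched and so escape the count.** That is not the course described. The Primary outcome and discontinuation sections call for management or referral once the overdose or QTc criteria are met. What stands is narrower: intervention is not defined, and some dose adjustment is left to clinical judgement, so it is unclear whether referral or observation alone counts.

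**A reader might infer that the whole hold rule depends on the filtered count.** Only the second trigger does. The first uses two serious events possibly related to participation in the first week, a lower bar with no intervention condition. In addition, Table 2 records overdoses needing intervention, hospitalizations and deaths at Day 7 with no relatedness condition.

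**Who judges relatedness** is not named. That unblinded study staff do so is an inference from the design, and the full protocol may settle it.

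**Restricting to drug-related events is defensible** in people who may continue street use, because an attribution-free count will include events from that use. This stands, and is why the wider count belongs beside the drug-related one and need not replace it.

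**Conclusion.** The concern holds in a limited form. The primary outcome is worded two ways across five places, and the narrower wording needs a relatedness judgement for which the article gives a rule only for induction somnolence or lethargy. No stated number is wrong: 92% is correct for a 5% problem in 50 participants. It describes the primary count only if every true event is counted. With 10%, 20% or 50% of events not counted, it would be 90.0%, 87.0% or 71.8%. Those shares are assumed, and the documents cannot say which, if any, applies. The 92% is also a statement about identifying a problem, and investigators could notice an event that they do not count.

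The analysis is descriptive, so no test is distorted. The documents do not support the stronger conclusion that the primary rate is biased downward or that the outcome must be replaced. This is a correction to make before the data are analysed, together with a fuller report of data already collected.

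**What to change.** 1. Reconcile the Abstract, Study objectives, Primary outcome, Data analysis and management, and Monitoring to one wording of the primary outcome.
2. For Days 1 to 7, report next to the drug-related count: (a) participants with any adverse event requiring intervention, regardless of attribution; and (b) participants meeting the protocol's own measured criteria, whether or not acted on. These are POSS 3 or 4, "respiratory rate below 8 breaths per minute, oxygen saturation below 92" per cent (or baseline, as worded there), and QTc above 500 ms or a rise of at least 60 ms. After the baseline ECG, QTc is measured only in methadone recipients, so give that component their denominator.
3. Before (b) is used, the investigators must clarify the saturation criterion, which names both 92% and the participant's baseline. Read literally, a one-point fall below baseline would qualify.
4. When the participant-count hold rule is reviewed, show the investigators the attribution-free count as well. Its limits stay as they are.

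Cost: a text amendment and extra rows in the safety table. Sedation score, vital signs and ECG are already scheduled in Tables 1 and 2. The downside is that the attribution-free rate may be higher than the drug-related rate and will include some events from continued street use, which the report should say.

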### Secondary outcomes

The secondary outcomes are related to efficacy and acceptability, specifically:Starting doses of oral OAT (methadone or SROM)Participant satisfaction with the SIFI procedureParticipant satisfaction with their current OUD treatmentProportion of participants who are retained on OAT after 1, 3, 6, and 12 monthsWithdrawal symptoms before and during induction phase, during early OAT phase, and during OAT follow-upOverdose, hospitalization, death at 1, 3, 6, and 12 months

Participant satisfaction with the SIFI procedure will be assessed during the immediate post-induction observation period, both quantitatively, using the single-item Medication Satisfaction Questionnaire [29, 30], and qualitatively, using three open-ended questions [31].

Participant satisfaction with their current OUD treatment (including safe supply, and recognizing that their current OUD treatment may be “none”) will be assessed before starting induction and during OAT follow-up visits using the single-item Medication Satisfaction Questionnaire [29, 30].

Withdrawal symptoms will be measured by the Clinical Opiate Withdrawal Scale (COWS) [32] before and during induction phase, during the early OAT phase, and during OAT follow-up.

Retention on OAT will be collected by participant self-report during the OAT follow-up visits and from the participant’s medical record. Any occurrence of overdose, hospitalization, and death during follow-up will be obtained from the participant’s medical record in the clinic electronic medical record (EMR) database.

## Treatment discontinuation and study discontinuation

Participants are free to withdraw from the study at any time without having to provide a reason for their decision. This will not affect their future medical care or other services that they receive at the clinic. If a participant decides to withdraw from the study, the research staff will not collect any further data from them, including data from the clinic EMR.

Discontinuation from study treatment may occur at the participant’s request or in the case of clinically significant adverse reactions and/or other safety reasons. If the participant experiences signs or symptoms consistent with opioid overdose during the induction procedure, the induction will be stopped and the clinic overdose response protocol will be implemented immediately. Ongoing management of the participant following an overdose event, including starting doses of OAT if appropriate, will be at the discretion of the clinic medical staff.

If a suspected opioid overdose occurs during the observation period after the first OAT dose or during a daily visit during the first week on OAT, the participant will be immediately referred to the clinic medical team for assessment and management, including adjustment of the OAT dose if deemed clinically necessary.

Participants receiving methadone who are found to have QTc prolongation (> 500 ms, or ≥ 60 ms increase from baseline) on their ECG on Day 3 or 7 and/or symptoms of possible TdP will be referred to the clinic medical team for prompt evaluation and management. Adjustment of methadone dose or transition to SROM may be offered as appropriate, based on clinical judgement and current Canadian OAT guidelines [27].

## Data analysis and management

The primary safety outcome will be assessed in the first instance by a descriptive analysis of adverse events requiring intervention during the induction and early OAT phases of the study. Secondary outcomes will be reported using descriptive and summary statistics. Participants’ responses to the treatment satisfaction questions will be summarized, and the results used to refine the SIFI procedure for future investigation.

Participants are assigned unique study codes that are not derived from or related to their personal information. Study-related documents, biological specimens, and ECG reports will be labelled only with the participant’s unique study code, and not with their name, initials, or other identifying information. All study documentation will be kept in a secure area in locked cabinets.

Files that contain personal identifying information are kept securely in locked offices in electronic form, and access to these files are password restricted to the principal investigator and a limited number of designated research team members. Identifying information collected on the questionnaires will be removed and stored separately from the questionnaire responses. Participant consents and contact information for follow-up will also be stored separately in a secure area in locked cabinets.

Electronic data will be stored on a secure server. For this study, clinical and sociodemographic information will be drawn from routinely collected clinic and administrative data in the clinic electronic medical record (EMR). Clinicians and research staff access the EMR via a roles-based, credentialed, secure portal to the EMR system.

Data in the clinic EMR database is under the custody of the British Columbia Centre for Excellence in HIV/AIDS ([name]) and its Director, [name] (a co-investigator on this study). The EMR database is stored on a secure server on the Centre’s network, protected by a defense-in-depth system including an industry-standard firewall prohibiting unauthorized entry. Strict measures are in place to protect the privacy of individuals in the database. The Centre also utilizes a suite of privacy and security policies to ensure the proper protection, management and integrity of all data. All data will be de-identified for study analyses to limit the potential for disclosure of identifying information.

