### Study population

#### Inclusion criteria

Age 19 years or olderOUD of any severity by DSM-5 Clinical Diagnostic criteria [18]Intentional use of unregulated fentanyl by any route (e.g. injection, inhalation) by participant self-reportUrine drug test (UDT) positive for fentanyl at screening or within 7 days prior to date of screening visit, to confirm the presence of fentanylClinical indication to start OAT with methadone or SROM, or recently started OAT and receiving daily doses of methadone ≤ 150 mg or SROM ≤ 1300 mg (demonstrated to be subtherapeutic for the individual as they are continuing to use unregulated fentanyl)If taking prescribed opioids for safer supply, willing to discontinue them starting on study Day 1 and for at least the first 7 days of the studyWilling and able to provide written informed consent for study participation

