	Before first OAT dose	1 h after first dose	2 h after first dose	3 h after first dose	Day 2	Day 3	Day 4	Day 5	Day 6	Day 7
HR, BP, RR, SpO2	x	x	x	x	x	x	x	x	x	x
POSS	x	x	x	x	x	x	x	x	x	x
COWS	x	x	x	x	x	x	x	x	x	x
Self-reported activity during previous 24 h					x	x	x	x	x	x
ECG	X^a^					X^b^				X^b^
MSQ for OUD meds	X^c^									x
MSQ + 3 questions re: SIFI				x						
Self-reported use of illicit opioids/other substances										x
UDT	X^c^									x
Overdose events req. intervention										x
Hospitalizations/death										x

*OAT* opioid agonist therapy, *UDT* urine drug test, *ECG* electrocardiogram, *POSS* Pasero opioid-induced sedation scale, *COWS* clinical opiate withdrawal scale, *HR* heart rate, *BP* blood pressure, *RR* respiratory rate, *SpO2* oxygen saturation, *MSQ* Medication Satisfaction Questionnaire, *SIFI* symptom-inhibiting fentanyl induction, *OUD* opioid use disorder

^a^For all participants, before start of IV fentanyl induction

^b^Only for participants receiving methadone

^c^At study screening

Methadone recipients who have QT prolongation at their follow-up ECG on Day 3 or Day 7 will be referred to the clinic team for assessment and management. For participants with a stable QTc and without evidence of opioid toxicity, methadone will be maintained at the same dose for the first 7 days.

For participants receiving SROM who meet all the following criteria, SROM doses may be increased by 100 mg every 24 to 48 h as clinically indicated, consistent with current local clinical guidelines [12].Presence of cravings and/or withdrawal symptomsNo evidence of opioid toxicity (e.g. excessive sedation/lethargy, respiratory depression, bradycardia)No evidence of SROM adverse events (e.g. constipation, nausea, vomiting, dyspepsia, abdominal pain, urinary retention, headache, dizziness, hypotension, diaphoresis, xerostomia, dental pain, dysphoria, insomnia) [24]

The magnitude of the SROM dose increase will be based on clinical judgement, taking into account the starting dose and severity of ongoing cravings or withdrawal symptoms.

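### The stated QT outcome counts only prolongation that required intervention, so threshold crossings that were merely evaluated, or a moderate QTc rise, need not appear in the safety result

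*Protocol article*

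**What the plan says.** Under Primary outcome, QT prolongation is one of the study drug-related adverse events that count, provided it required intervention on study days 1 to 7. Data analysis and management carries the same condition into the analysis: "The primary safety outcome will be assessed in the first instance by a descriptive analysis of adverse events requiring intervention during the induction and early" (treatment phases).

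The ECG schedule is fuller than that outcome. Table 2 places the baseline ECG as follows: "For all participants, before start of IV fentanyl induction". Afterwards, "an ECG will be repeated on OAT Days 3 and 7 for participants receiving methadone". A numerical limit is given: "Any occurrence of QTc prolongation (> 500 ms, or ≥ 60 ms increase from baseline) and/or symptoms consistent with TdP will be managed promptly". The same section ties the hazard to dose, since participants are to be "advised during the informed consent process that the risk of arrhythmia is increased with higher doses of methadone".

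Under Treatment discontinuation and study discontinuation, a participant over the limit is referred to the clinic team. A dose adjustment or a change of agent is possible but left to judgement. The Secondary outcomes section lists efficacy and acceptability measures and contains no QTc or ECG variable.

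**The concern.** Whether a QT finding enters the primary outcome depends on two things: what the ECG shows and what the clinician does about it. The article fixes the referral but does not say whether referral, or evaluation with no change of treatment, amounts to intervention. Two participants with the same QTc could be classified differently. A systematic rise that leaves everyone under the limit would not register in any stated outcome.

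This matters because the pilot's stated goal is to find unforeseen safety problems and inform a larger study. The strategy is expected to give higher-than-standard methadone starting doses, and the protocol itself says that arrhythmia risk grows with dose. A report of no QT events requiring intervention could be read as no QT effect. The second enrolment-hold criterion under Monitoring uses the same intervention-dependent count.

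**Working it through.** **The plan's own figure.** The design is an "open-label, single arm, prospective clinical trial with a planned sample size of 50", and for a problem with 5% prevalence "it will be identified with 92% confidence in a pilot study including 50 participants". This reproduces: 1 − 0.95^50 = 0.923. It applies to a problem that can be seen in all 50. Follow-up ECGs cover methadone recipients only; if there were 25 of them, a QT problem with 5% prevalence among them would be seen at least once with probability 1 − 0.95^25 = 0.723.

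**Route 1: a crossing that is recorded but not counted.** No arithmetic applies; three statements are set side by side.
- The outcome needs an event that required intervention.
- A crossing leads to referral, evaluation and management.
- Adjusting the dose or changing the agent is optional.

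A crossing that is evaluated and followed without a treatment change is in the data, but the article does not settle whether it is in the outcome.

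**Route 2: a rise below the limit.** The article gives neither the number on methadone nor the SD of QTc change, so these are assumptions: n = 25 (range 15 to 50) and SD = 20 ms (range 15 to 25), with normally distributed changes. The calculation uses one follow-up ECG per person and ignores the 500 ms limit.

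- Chance that one person rises by 60 ms or more: p = 1 − Φ((60 − mean)/SD).
- Chance that nobody does: (1 − p)^n.
- Example, mean 20 ms: (60 − 20)/20 = 2, p = 0.0228, (1 − p)^25 = 0.563.

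| True mean rise | p, SD 20 | Nobody in 25, SD 20 | Nobody in 25, SD 25 to SD 15 |
|---|---|---|---|
| 10 ms | 0.0062 | 86% | 56% to 99% |
| 20 ms | 0.0228 | 56% | 24% to 91% |
| 30 ms | 0.0668 | 18% | 5% to 56% |
| 40 ms | 0.1587 | 1% | 0.3% to 9% |

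Over the whole range of n and SD, the chance of no crossing at a 20 ms mean rise runs from 6% to 94%; at 40 ms it is at most 24%.

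**Allowing for two follow-up ECGs.** If Days 3 and 7 had the same mean and SD and were independent within a person, the exponent would be 50: (1 − p)^50 = 32% at 20 ms and 3% at 30 ms. Two changes measured from one baseline should be positively correlated, so under these assumptions the answer lies between 32% and 56% at 20 ms, and between 3% and 18% at 30 ms.

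**What the same ECGs could show.** The 95% half-width for the mean change is 1.96 × 20/√25 = 7.8 ms, or 8.3 ms with the t quantile. Over the assumed ranges, the t-based half-width is 4.3 to 13.8 ms. A 20 ms mean rise would be clearly visible at the central assumptions.

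**The case against.** The best case for the plan has four parts.

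- **This is a condensed article with no SAP shown.** A table of QTc change by visit is ordinary SAP content, so its absence is no error. That is right, and the point does not rest on it. The condition that an event required intervention is stated in the outcome definition, and an SAP that follows the definition inherits it.
- **The analysis text describes a first step.** A reader might infer that QTc values are barred from analysis, that they are to be cut to yes/no at the limits, or that participants already on methadone will be pooled with the rest. The article says none of this. The limits are there to trigger management, the event list is open-ended, and pooling is not mentioned.
- **The limit is said to be managed promptly, so every crossing may be an intervention.** That reading is possible. The article does not adopt it, and the optional wording on dose and agent leaves the other reading open.
- **The illustration leans towards missed events.** It does: it uses one ECG instead of two and omits the 500 ms limit. A large rise would seldom go unnoticed.

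A reader might also fault the baseline, since a participant may enter having "recently started OAT and receiving daily doses of methadone ≤ 150 mg or SROM ≤ 1300 mg" and so have an on-methadone ECG before induction. The criticism does not hold. For an intervention that changes the dose, the increment from that ECG is the relevant contrast, and the 500 ms limit applies whatever the baseline. Prior methadone use is worth showing, but the baseline is not wrong.

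**Conclusion.** The point holds in limited form. In the outcomes and analyses stated, QTc counts only as a drug-related event that required intervention, and that condition is not settled for a crossing that leads to evaluation alone. Such a crossing, or a moderate systematic rise, need not appear in the safety result although the ECGs exist.

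The exposure is to mean rises of roughly 10 to 30 ms. At the central assumptions the chance of no 60 ms crossing falls from 86% to 18% over that range, and is lower once the second ECG is allowed for. The documents do not support the inference that a large QTc effect would be hidden. All these figures rest on an assumed number of methadone recipients, SD and mean shift, and serve as illustration only. The uncertainty over crossings that are evaluated but not treated needs none of those assumptions.

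**What to change.** In Secondary outcomes and in Data analysis and management, add a descriptive QTc safety outcome for methadone recipients:

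- mean change in QTc from the pre-induction ECG to Day 3 and to Day 7, each with a 95% confidence interval;
- the number over 500 ms and the number with a rise of 60 ms or more, whether or not intervention followed;
- both shown descriptively by methadone use at entry.

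No further QTc categories and no dose regression are needed for a pilot of this size. The primary outcome can stay as it is, and the management rules stay as written. The cost is a few lines of text and one extra table, with no new ECGs, visits or participants. The article reports that recruitment is ongoing, so the addition can be made before the results are analysed.
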